Participants will be followed up monthly for four months. Clinically, blood pressure may be controlled with medication within four to six weeks [33]. For type II diabetes, although traditionally changes in HbA1c are assessed every three months, emergent evidence suggests clinically relevant changes may occur as early as one month [34]. Based on these data, four months was deemed appropriate to observe clinical improvements as well as being a sufficient period to test the system. Clinic visits may be face-to-face or virtual as appropriate. If a dosage change is required at a clinic visit, hypertensive participants will be asked to monitor their ambulatory blood pressure for a single six-hour period at home (once hourly). A six-hour ambulatory blood pressure recording is equivalent to a twenty-four-hour reading [35]. Patients will then continue to monitor blood pressure twice daily, morning and evening, for up to seven days. Following any change of type II diabetic medications, patients will be asked to wear a continuous glucose monitoring device for a minimum of seven days at home (the maximum wear time is fourteen days). Monitoring will commence fifteen days after the dose change is initiated (for either hypertensives or type II diabetics), so a steady state can be reached before assessment. These data will feed back into the CURATE.AI system, and further recommendations on dose adjustment will be generated if required. The treating physician will regularly review remote monitoring data for safety. If the patient’s medication is changed entirely, recalibration with CURATE.AI is required. At the last clinic visit, patients will be interviewed using a semi-structured survey on their experiences with the CURATE.AI system. 

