Compliance with clinic follow-up will be calculated based on the number of scheduled sessions compared to attendance. Compliance with home monitoring will also be determined by remote receipt of data at scheduled time points. The proportion compliant with the home-monitoring schedule and the proportion of patients who drop out from the study will be reported. The number of disagreements between the CURATE.AI dosing recommendations and the physician’s opinion will be quantified. Success of the alignment on dosing decisions is defined as agreement with ≥70% of dosing decisions generated by CURATE.AI. The proportion of participants reaching this criterion will be derived. We will also summarise the reasons for disagreement and the magnitude of differences in dosing decisions, if it occurs. A sub-analysis will be conducted for participants whose dosing decisions were all based on CURATE.AI recommendations versus those who had one or more dosing decisions overridden by the treating physician. The purpose is to explore whether adherence to CURATE.AI confers an advantage in achieving clinical outcomes. Significance will be set at *p* < 0.05.

For interviews, audio recordings of the interview will be transcribed and translated into English (if necessary). A second independent researcher will check the accuracy of the translation. Data will be analysed using a thematic analysis method. Data will be coded according to the meaning of the sentences, followed by developing sub-themes and main themes. Qualitative data will also be organised according to the framework domains (Table 2).

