**Other data captured:**					
Demographics	X				
Weight, BMI, hip-waist ratio	X	X	X	X	X
Medical history (morbidities, medication)	X				
Renal function	X				X
Liver function	X				X
Details of physical activity (16 items)	X				X
Details of diet (26 items)	X				X
Medication adherence (9 items)	X				X
Change in medications	X	X	X	X	X
Disagreements between CURATE.AI and physician	X	X	X	X	X
Patient survey					X

^a^ Home-monitoring may be scheduled 15 days after dose change, if indicated.

**Table 2 ijerph-19-08979-t002:** Modified NASSS and AI framework domains and associated data sources [36,37].

NASSS Domain	Data Sources
1A/1B: What is the nature of the condition?/What are the relevant sociocultural factors and comorbidities?	Patient profiles and patient interviews
2A: What are the key features of the technology?	The algorithm and desired features identified in staff interviews
2B: What kind of knowledge does the technology bring into play?	Application of algorithm in chronic disease care, and staff and patient interviews
2C: What knowledge and support are required to use the technology?	Patient and staff interviews
3B: What is the technology’s desirability, efficacy, safety, and cost effectiveness?	Study outcomes, and patient and staff interviews
4A: What changes in staff roles, practices, and identities are implied?	Staff interviews
**AI Framework Domain**	**Data Sources**
Data form: Data access, the structure of data, appropriateness of data, data plan	Evaluation of data collection from medical record data, clinic assessments, and home-monitoring
Model development form: Determine the best algorithm type, scalability of the algorithm	Algorithm development through retrospective analysis of medical record data
Model development build: Pilot test performance of the algorithm	Study outcomes and staff interviews

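### The sub-analysis of patients with all decisions followed versus any override can show a difference when overriding has no effect, because group membership depends on how many decisions a patient has

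*Protocol article*

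**What the plan says.** Section 2.3.5 (Data Analysis) plans a comparison of "participants whose dosing decisions were all based on CURATE.AI recommendations versus those who had one or more dosing decisions overridden by the treating physician". Its aim is stated in the next sentence: "The purpose is to explore whether adherence to CURATE.AI confers an advantage in achieving clinical outcomes". The paragraph then closes with "Significance will be set at *p* < 0.05". No landmark time, per-decision rate or allowance for the number of decisions is given.

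Four other parts of the article bear on the groups:

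- **Starting point.** Patients already controlled at baseline are excluded (section 2.3.1), so everyone starts uncontrolled.
- **Outcome window.** Control at four months and days to first control (sections 2.3.2 and 2.3.5) cover the period in which overrides accumulate.
- **Number of decisions.** In section 2.3.3, once home-monitoring data have been fed back, "further recommendations on dose adjustment will be generated if required". That monitoring itself follows a change: "If a dosage change is required at a clinic visit, hypertensive participants will be asked to monitor their ambulatory blood pressure", and for diabetes "Following any change of type II diabetic medications, patients will be asked to wear a continuous glucose monitoring device". The Table 1 footnote adds "Home-monitoring may be scheduled 15 days after dose change, if indicated". Table 1 also lists disagreements between CURATE.AI and the physician at baseline and at all four visits.
- **Override.** The physician's opinion prevails whenever it differs, the reason is recorded, and the patient stays in the study (section 2.3.3).

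**The concern.** The exposure is all-or-none and is known only at the end of follow-up. A patient with one decision has one chance to be overridden. A patient with five has five. If patients who reach control early face fewer decisions, a good outcome helps to place them in the all-followed group, and cause and effect run backwards. Dropout also shortens the list of decisions, so patients who leave early are likewise more often classed as all followed.

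Separately, an override is a clinical judgement. If physicians override more often in patients whom they expect to do badly, or in those they expect to do well, the groups differ in prognosis before any effect of the decision.

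What is at stake is the reading of this one comparison. It is the only within-study contrast that the article links to a benefit of following the algorithm, and the Discussion says that the data will inform a later efficacy evaluation.

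**Working it through.** The article gives no figure for this sub-analysis, so there is nothing to reproduce. The check asks how large the contrast is when overriding has no effect on control.

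**Inputs from the article.** All patients start uncontrolled; baseline plus four monthly visits; 20 patients per disease, analysed separately.

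**Assumptions, not in the article.** Override probability per decision q = 0.1 to 0.3, unrelated to prognosis. Probability of first control at each monthly visit h = 0.2 to 0.3. Control lasts, and there is no dropout unless stated.

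**Step 1: chance of no override with k decisions.** This is (1 - q)^k. At q = 0.2 it is 0.80 for k = 1, 0.64 for 2, 0.51 for 3, 0.41 for 4 and 0.33 for 5.

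**Step 2: reading A, decisions stop once controlled.** A patient first controlled at visit k has k decisions (baseline to visit k - 1). A patient never controlled has 4.

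- P(all followed and controlled) = sum over k = 1 to 4 of h(1 - h)^(k-1)(1 - q)^k
- P(all followed, not controlled) = (1 - h)^4 (1 - q)^4

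With h = q = 0.2:

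- first term: 0.16 x (1 + 0.64 + 0.4096 + 0.2621) = 0.3699
- second term: 0.4096 x 0.4096 = 0.1678
- P(all followed) = 0.5377
- control if all followed: 0.3699 / 0.5377 = 68.8%
- overall control: 1 - 0.8^4 = 0.5904
- control if any override: (0.5904 - 0.3699) / (1 - 0.5377) = 47.7%
- spurious difference: +21.1 points

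**Step 3: reading B, a decision at all five time points for everyone, plus one after each home-monitoring period while uncontrolled.** A patient controlled at visit k has 5 + k decisions, and one never controlled has 9. Both terms of step 2 are multiplied by (1 - q)^5 = 0.3277. Control if all followed stays at 68.8%. P(all followed) becomes 0.5377 x 0.3277 = 0.1762. Control if any override is (0.5904 - 0.3699 x 0.3277) / (1 - 0.1762) = 57.0%. The difference is +11.8 points.

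**Step 4: reading C, exactly five decisions for everyone.** P(all followed) is (1 - q)^5 whatever the outcome, so the difference is 0.

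| h, q | A: all followed vs any override | A: difference | B: difference | C: difference |
|---|---|---|---|---|
| 0.2, 0.1 | 63.6% vs 46.1% | +17.6 | +8.1 | 0 |
| 0.2, 0.2 | 68.8% vs 47.7% | +21.1 | +11.8 | 0 |
| 0.2, 0.3 | 74.5% vs 49.4% | +25.1 | +16.5 | 0 |
| 0.3, 0.1 | 79.6% vs 63.7% | +15.9 | +6.6 | 0 |
| 0.3, 0.2 | 83.3% vs 65.4% | +17.9 | +9.1 | 0 |
| 0.3, 0.3 | 87.1% vs 67.1% | +20.0 | +12.0 | 0 |

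Differences are in percentage points, taken before rounding. If uncontrolled patients also have a decision at Visit 4, the second term of step 2 becomes (1 - h)^4 (1 - q)^5, and reading A rises to +21.6 to +33.5.

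**Step 5: dropout.** Let 5% leave before each visit and count as not controlled, with q = 0.2 and h = 0.25. Under reading C:

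- completers: 0.95^4 = 0.8145; control among them: 1 - 0.75^4 = 0.6836
- P(all followed) = 0.8145 x 0.3277 + 0.05 x (0.8 + 0.95 x 0.64 + 0.9025 x 0.512 + 0.8574 x 0.4096) = 0.2669 + 0.1111 = 0.3780
- control if all followed: 0.2669 x 0.6836 / 0.3780 = 48.3%
- control if any override: (0.8145 x 0.6836 - 0.1825) / 0.6220 = 60.2%
- difference: -11.9 points

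The same enumeration gives -5.9 under reading B and +12.1 under reading A (+16.7 with the Visit 4 decision).

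**Step 6: significance with 20 patients.** In 20,000 simulated studies per scenario of the table under reading A, Fisher's exact test gave p < 0.05 in 6 to 10%, although following had no effect.

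**The case against.** The strongest reply is that the article does not say that controlled patients stop having decisions. The words about further recommendations being generated if required concern home-monitoring data between visits. Section 2.3.3 intends recommendations to be produced live within clinic visits, and Table 1 records disagreements at every visit. Keeping the dose unchanged may count as a decision. This stands: reading A is only one possibility. It does not remove the problem, because the extra recommendations are still conditional, which is reading B. Only equal numbers for every patient give zero, and the article does not provide for that.

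A reader might infer that the comparison must favour adherence. The documents do not support this. Dropout pulls the other way and can reverse the sign. Nor does the article say that physicians override when a patient does badly, so confounding by the reason for override is a possibility, not a stated fact.

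It is also fair that the sub-analysis is exploratory, that sections 2.3.2 and 3 disclaim efficacy, that reasons for disagreement will be summarised, and that no decision rule hangs on the result. The p < 0.05 sentence may be a general threshold, since no test is named for this comparison. All of this limits the harm. But the disclaimers concern the absence of a control group and do not mention this bias. Summarising reasons does not adjust for it, and recruiting more patients would not remove it.

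**Conclusion.** The concern holds in a limited form. As written, the contrast mixes any effect of following CURATE.AI with the number of decisions, the handling of dropouts and the physician's reasons for overriding. It cannot answer the question set for it.

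With no true effect and the assumed rates, the spurious difference runs from about +16 to +25 points (decisions stop at control), through about +6 to +16 (every visit plus extra decisions), to 0 (equal numbers). It was about -6 and -12 under the last two readings in the dropout example. Neither direction nor size can be fixed from the documents, because they give no override, control or dropout rates and do not define a dosing decision.

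It should be fixed, but it is not critical: no feasibility criterion depends on it. A reader might infer that it would mislead a later efficacy trial. The article says only that the data will inform such an evaluation, not that this contrast will set any design value.

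**What to change.** 1. Remove the patient-level significance test and the aim of judging whether adherence confers an advantage.
2. Report the number of decisions and of overrides per patient, by disease group, and say whether an unchanged dose counts as a decision.
3. For decisions with a later assessment (baseline to Visit 3), describe the change in blood pressure or glucose at the next assessment after followed and after overridden decisions. Adjust for the value just before the decision and allow for clustering by patient (GEE or a patient random effect). If overrides are too few for a model, use simple description.
4. Give the estimate with a 95% CI, labelled as descriptive and confounded by the reason for override.

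**Cost.** A change of wording and a slightly more involved analysis. Blood pressure, glucose and disagreements are already recorded at every visit in Table 1, and the reasons are collected. Intervals will be wide: 20 patients x 4 visits gives at most 80 visit decisions per disease group, of which 8 to 24 would be overridden at the assumed 10-30%.

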## 3. Discussion

We aim to establish if the CURATE.AI system can practically be used for chronic disease patients and how it can be best operationalised through this feasibility study. We will explore if users find the system acceptable, identify factors that can help or hinder its use, and understand its potential for scaling. In addition, we will investigate ways to improve the algorithm. For example, the inclusion of other variables (i.e., patient characteristics), the simultaneous optimisation of multiple drugs, and the incorporation of other AI algorithms. The data generated from this study will inform the development of the CURATE.AI system and a future efficacy evaluation. Through the development of this application, we hope it may be possible to optimise dosing more rapidly, prevent adverse reactions, and reduce the burden of therapy.

### Potential Strengths and Limitations of the Study

We have chosen a mixed-method approach to explore the practicalities of using a precision drug dosing algorithm in clinical practice. Including qualitative methods, in addition to clinical outcomes, will bring a greater breadth and depth of understanding as to the use of CURATE.AI in clinical practice. However, there are limitations. This is only a feasibility study, and there is no control group. We will not establish the efficacy of the intervention from this study alone. Future randomised controlled trials will be needed to understand the clinical impact of CURATE.AI. Furthermore, the current iteration of CURATE.AI is not integrated within the existing electronic medical record systems. If CURATE.AI were to scale, workflows need to be developed so that data can seamlessly enter the algorithm. Qualitative interviews will explore how CURATE.AI could be adopted into existing workflows and systems. 

## 4. Conclusions

In conclusion, this study is the first in a programme of research that will seek to understand if CURATE.AI can effectively be used to manage chronic disease patients in the clinical setting.

## Figures and Tables

**Figure 1 ijerph-19-08979-f001:**
[figure not shown]
Patient flow.

**Table 1 ijerph-19-08979-t001:** Study procedures and timepoints.

Data Variables	Baseline ^a^	Visit 1 ^a^	Visit 2 ^a^	Visit 3 ^a^	Visit 4
**CURATE.AI variables:**					
Retrospective dose-response data mined	X				
Hba1C ^a^ or blood glucose	X	X	X	X	X
Blood pressure	X	X	X	X	X
**Other data captured:**					
Demographics	X				
Weight, BMI, hip-waist ratio	X	X	X	X	X
Medical history (morbidities, medication)	X				
Renal function	X				X
Liver function	X				X
Details of physical activity (16 items)	X				X
Details of diet (26 items)	X				X
Medication adherence (9 items)	X				X
Change in medications	X	X	X	X	X
Disagreements between CURATE.AI and physician	X	X	X	X	X
Patient survey					X

^a^ Home-monitoring may be scheduled 15 days after dose change, if indicated.

**Table 2 ijerph-19-08979-t002:** Modified NASSS and AI framework domains and associated data sources [36,37].

NASSS Domain	Data Sources
1A/1B: What is the nature of the condition?/What are the relevant sociocultural factors and comorbidities?	Patient profiles and patient interviews
2A: What are the key features of the technology?	The algorithm and desired features identified in staff interviews
2B: What kind of knowledge does the technology bring into play?	Application of algorithm in chronic disease care, and staff and patient interviews
2C: What knowledge and support are required to use the technology?	Patient and staff interviews
3B: What is the technology’s desirability, efficacy, safety, and cost effectiveness?	Study outcomes, and patient and staff interviews
4A: What changes in staff roles, practices, and identities are implied?	Staff interviews
**AI Framework Domain**	**Data Sources**
Data form: Data access, the structure of data, appropriateness of data, data plan	Evaluation of data collection from medical record data, clinic assessments, and home-monitoring
Model development form: Determine the best algorithm type, scalability of the algorithm	Algorithm development through retrospective analysis of medical record data
Model development build: Pilot test performance of the algorithm	Study outcomes and staff interviews

## Data Availability

Not applicable.
